### 9.1 Measurement of Outcomes

#### 9.1.1. Time-to-event outcomes

Overall survival will be measured as time from randomization to death from any cause.

## **10.0 STATISTICS AND SAMPLE SIZE CALCULATIONS**

### 10.1 Randomization

Patients will be randomized in a 1:1 ratio between Arm 1 and Arm 2. The sample size allows for one stratification factor at randomization: the prescribed RT dose. Randomization will occur in permuted blocks, with the block size known only by the statistician.

A randomized design is indicated for the following reasons:

1. Historically, esophagitis following RT for lung cancer has been measured mostly

through CTCAE, and such data may not provide an appropriate control due to various sources of biases from patient selection, technical RT factors and other comparisons. Thus randomization will provide a more appropriate control group to serve for the experimental arm, particularly when using the FACT-G and cancer subscales.

2. The sample size calculated allows for adequate power to detect a clinically meaningful change in esophageal quality of life

### 10.3 Stratification

The sample size calculated allows for one stratification factor at randomization, which will be the prescribed dose (20 Gy/5# vs. 30 Gy/10#).

### 10.4 Sample size calculation

Regarding the primary endpoint, a change in ECS score of 2 to 3 points is considered clinically relevant. We will assume there will be a moderately large effect size (0.65), and a non-responder rate of 15% (5). Using a two-sided, independent-sample t-test with an alpha level of 0.05 and power of 80%, to detect a clinically relevant ECS change in the experimental arm, 90 patients will be required (45 in each arm).

We anticipate that 1-2 patients could be accrued each month at each participating institution, yielding approximately 30 patients per year. The study thus projects accrual over 4 years with 12 months of additional follow-up. Accrual for the sample size calculated is feasible in the Canadian multi-institutional context.

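### Section 10.4 sizes the trial on a standardised effect of 0.65 but states the 80% power as power for a 2 to 3 point ECS change, with no SD to link the two

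*Protocol*

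**What the plan says.** Protocol section 10.4 sets a threshold in points: "a change in ECS score of 2 to 3 points is considered clinically relevant". The sample size inputs that follow have no units: "We will assume there will be a moderately large effect size (0.65), and a non-responder rate of 15" per cent. The test is then specified: "Using a two-sided, independent-sample t-test with an alpha level of 0.05 and power of 80" per cent. The target of that power is given in words, not as 0.65: "to detect a clinically relevant ECS change in the experimental arm, 90 patients will be required (45 in each arm").

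Section 10.1 repeats the claim as a reason for randomizing: "The sample size calculated allows for adequate power to detect a clinically meaningful change in esophageal quality of life".

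Three other places bear on it:

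- Section 10.5 makes the primary analysis a Student's t-test on the 2-week score, without adjustment for baseline.
- Section 10.6 counts a 2-point change from baseline, patient by patient, as clinically significant.
- Appendix 2 schedules the FACT-E before radiotherapy, so a baseline ECS is available.

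No SD for the ECS, observed or assumed, appears in the protocol.

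**The concern.** A t-test sized on 0.65 has its stated power for a difference of 0.65 SD. Whether that is 2 points, 3 points or 6 points depends entirely on the SD. Section 10.4 defines relevance in points, computes in SD units, and then reports the power as if it belonged to the points. A reader of sections 10.1 and 10.4 would take the trial to have an 80% chance of detecting a true 2 to 3 point difference, and nothing in the protocol shows that.

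What is at stake is how a non-significant result is read. If the SD exceeds the implied values, such a result could be taken to exclude a relevant benefit when the trial was not powered to do so. The provision in section 10.6 for changing the accrual target is affected too. It compares the measured difference with the one estimated in the sample size calculation, but that calculation gives neither a difference in points nor an SD.

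**Working it through.** **Inputs.** Section 10.4: standardised effect d = 0.65, two-sided alpha 0.05, power 80%, non-response 15%, relevant change 2 to 3 points. Section 10.1: allocation 1:1. Appendix 4: 17 ECS items scored 0 to 4, so a range of 0 to 68 (counted from the questionnaire).

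**Step 1: reproduce the stated 90.** Normal approximation: n per arm = 2 × (1.960 + 0.842)² / 0.65² = 37.2, rounded up to 38. Allowing for non-response: 38 / 0.85 = 44.7, rounded up to 45 per arm, 90 in total. This matches. The exact noncentral t calculation gives 79.9% power at 38 per arm. It would ask for 39, or 46 per arm after inflation (92 in total), a difference too small to matter.

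**Step 2: the SD needed for 0.65 to mean 2 to 3 points.** SD = difference / 0.65.

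- 2 points: 2 / 0.65 = 3.08, which is 4.5% of the 0 to 68 range.
- 3 points: 3 / 0.65 = 4.62, which is 6.8% of the range.

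**Step 3: can one SD serve both ends?** At SD 4.62, 3 points has d = 0.65 and the intended 80% power. At the same SD, 2 points has d = 2 / 4.62 = 0.43 and 46% power. The claim covers the whole 2 to 3 point range only if the SD is about 3.1 or less. This step needs no outside figure.

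**Step 4: power over a range of SDs.** Every SD here is an assumption. Two-sided t-test at 0.05, 38 evaluable per arm, noncentrality = (difference / SD) × √(38/2).

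| Assumed SD | Power, 2 points | Power, 3 points | 0.65 SD in points |
|---|---|---|---|
| 3.08 | 79.9% | 98.7% | 2.0 |
| 4 | 57.6% | 89.7% | 2.6 |
| 4.62 | 46.2% | 79.9% | 3.0 |
| 5 | 40.6% | 73.3% | 3.25 |
| 6 | 30.0% | 57.6% | 3.9 |
| 8 | 18.9% | 36.5% | 5.2 |
| 10 | 13.8% | 25.2% | 6.5 |

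**Step 5: what baseline adjustment could recover.** Adjusting for baseline ECS multiplies the SD by about √(1 − ρ²), where ρ is the correlation between baseline and 2-week ECS. The protocol gives no ρ. As an illustration at SD 6, power for 3 points goes from 58% to about 62% if ρ = 0.3, 70% if ρ = 0.5 (6 × 0.866 = 5.20) and 85% if ρ = 0.7.

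**The case against.** The strongest defence is that nothing has been miscalculated. The 90 follows from its inputs, and an effect size may properly be specified in SD units. This stands: the defect lies in what the 80% is said to be for, not in the sample size.

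A reader might go further and infer that an SD of 3.1 to 4.6 on a 0 to 68 scale is implausibly small, that true power is therefore far lower, and that a 2 to 3 point benefit would probably be missed. The protocol does not support this, because it contains no ECS SD. An item-level argument only exchanges one assumption for two. The SD of a 17-item sum is s × √(17 × (1 + 16r)), with item SD s and mean inter-item correlation r. With s = 1 it is 4.1 at r = 0 and 8.5 at r = 0.2. But an item answered 80% in the best category, 15% one below and 5% two below has s = √(0.35 − 0.25²) = 0.54, and at r = 0.2 the total SD is then about 4.5. Such ceiling effects are possible: many items concern swallowing, the patients have lung cancer, and severe esophageal disorders are excluded.

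Two further points have weight. First, the 2 to 3 points may be meant as a within-patient threshold, since sections 10.4 and 10.6 both speak of change. The power table would then answer a question the protocol did not clearly ask. Section 10.4 nevertheless makes this change the target of a between-arm test, so the ambiguity itself needs resolving. Second, section 10.6 lets the data safety monitoring committee recommend a different accrual target after the 30-patient look. That is a partial safeguard, but it does not supply the missing SD.

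**Conclusion.** The point holds as a defect in the power statement. Sections 10.1 and 10.4 claim adequate power for a clinically relevant change of 2 to 3 points, while the calculation supports only 80% power for 0.65 SD. The two agree at 2 points if the SD is at most 3.08, and at 3 points if it is at most 4.62. At the larger of these SDs, power for 2 points is 46%, so the claim does not cover its own range unless the SD is about 3.1 or less.

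Beyond that, power for 2 to 3 points is unknown, not shown to be low. Over assumed SDs of 4 to 10 it runs from 58% down to 14% for 2 points, and from 90% down to 25% for 3 points. These figures assume 38 evaluable patients per arm, the unadjusted t-test of section 10.5, and that 2 to 3 points is meant as a between-arm difference. The size of 90 is not in error for the effect it was computed from.

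**What to change.** 1. Restate section 10.4 along these lines: *Ninety patients give 80% power for a between-arm difference of 0.65 SD in 2-week ECS. This corresponds to 2 points if the SD is 3.1 and to 3 points if it is 4.6; power for 2 to 3 points is lower if the SD is larger.*
2. Give the assumed SD and its source, and hence the difference in points that 0.65 stands for. This also gives the accrual provision in section 10.6 a reference value.
3. Say whether 2 to 3 points is a within-patient or a between-arm threshold.
4. Qualify the power statement in section 10.1 to match.
5. In section 10.5, replace the unadjusted t-test with a comparison of 2-week ECS adjusted for baseline ECS, and read the confidence interval for the difference against 2 to 3 points.

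Items 1 to 4 are changes of wording. Item 5 changes the primary analysis, so it should be made by amendment before outcome data by arm are seen; it uses data already scheduled in Appendix 2. The cost is a less favourable stated figure. No extra patients are needed.

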### 10.5 Analysis plan

Patients will be analyzed according to the intention-to-treat principle (analyze in the groups to which they are assigned).

#### ***Primary Endpoint***

Esophageal quality of life will be calculated by tabulating FACT-E scores at 2 weeks, with differences between groups tested using the Student's t-test.

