#### ***Secondary Endpoints***

Additional QoL endpoints will be analyzed by compiling relevant EQ-5D values, FACT subscale and trial outcome index (TOI) scores. Treatment arm differences will be analyzed using linear mixed-effects models. Survival will be calculated Kaplan-Meier method with differences compared using the stratified log-rank test. Differences in rates of grade 2 or higher toxicity between groups will be tested using the Fisher's Exact test. Differences in the number of cycles of further systemic therapy will be tested using the student's t-test. EQ-5D measurements will be converted into utilities to inform cost-effectiveness/utility analyses. Finally dosimetric comparison of GTV, PTV, as well as standard pulmonary and esophageal metrics will be compared using the student's t-test.

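### The primary test is an unadjusted t-test on the 2-week score alone, so it ignores the scheduled pre-RT ECS and can be biased if missing forms are tied to the score and differ by arm

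*Protocol*

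**What the plan says.** - **Primary analysis (section 10.5, Primary Endpoint):** "tabulating FACT-E scores at 2 weeks, with differences between groups tested using the Student's t-test". No covariate and no other visit is named.
- **Sample size (section 10.4):** a two-sided two-sample t-test, alpha 0.05, power 80%, standardised effect 0.65, and "a non-responder rate of 15" percent, giving 90 patients (45 per arm). The term non-responder is not defined. The same section says that "a change in ECS score of 2 to 3 points is considered clinically relevant" and gives no SD.
- **Analysis set (section 10.5):** "Patients will be analyzed according to the intention-to-treat principle (analyze in the groups to which they are assigned").
- **Other quality-of-life scores (section 10.5, Secondary Endpoints):** "Treatment arm differences will be analyzed using linear mixed-effects models".
- **Data available (Appendix 2):** FACT-E is scheduled before RT, at 2, 4 and 8 weeks after RT, and at 3, 6 and 12 months. Forms may be completed by telephone.

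**The concern.** The primary endpoint gets a weaker analysis than the secondary ones, although the data for a better one are already being collected. A patient without the 2-week form adds nothing to the named test, even if a pre-RT and a 4-week score exist.

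This matters because missing forms may not be random here. Patients are palliative with ECOG 0-3, and section 1.1 says that esophagitis can lead to pain, weight loss and hospital admission. The outcome being measured can therefore keep a patient from answering, and the trial expects that outcome to differ by arm. If so, the responders in the two arms are differently selected. The comparison could hide a benefit (more ill controls missing) or inflate one (more ill ES-IMRT patients missing).

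Apart from bias, leaving out the baseline score gives up precision that costs nothing to obtain.

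**Working it through.** **1. The plan's own figure.** Inputs from section 10.4: d = 0.65, two-sided alpha 0.05, power 80%, non-response 15%.

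- Normal approximation: n = 2(1.960 + 0.842)² / 0.65² = 37.2, so 38 per arm. Then 38 / 0.85 = 44.7, so 45 per arm and 90 in total.
- Noncentral t: 38.14 per arm, and 38.14 / 0.85 = 44.9, so again 45. Rounding to 39 first gives 46 per arm, or 92.

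Without the division by 0.85 the total would be 76 to 78. The stated 90 therefore treats the 15% as having no usable primary score.

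**2. Expected loss and power.** 0.15 × 90 = 13.5 patients, leaving 76.5, or 38.25 per arm. Power at d = 0.65 is then 80.1%. The expected loss is already paid for.

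**3. Simple bias formula.** Let p be the share missing in an arm and d the amount, in SD, by which its missing patients would have scored worse than its responders. The shift in the estimate (ES-IMRT minus control) is p_E·d_E − p_C·d_C. All splits and d values are assumptions.

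| Missing, ES-IMRT / control | d | Shift (SD) | Expected estimate if truth is 0.65 |
|---|---|---|---|
| 15% / 15% | equal in both arms | 0 | 0.65 |
| 10% / 20% | 0.5 to 1 in both | 0.05 − 0.10 = −0.05 to 0.10 − 0.20 = −0.10 | 0.60 to 0.55 |
| 20% / 10% | 0.5 to 1 in both | +0.05 to +0.10 | 0.70 to 0.75 |
| 15% / 15% | 1 in control only | −0.15 | 0.50 |

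With no true effect, the third row gives a two-sided type I error of about 5.5% to 7.2% (SD held at 1). If the 2 to 3 points are taken to be the 0.65 effect, the SD is 2/0.65 = 3.1 to 3/0.65 = 4.6 points, so a shift of 0.05 to 0.10 SD is about 0.15 to 0.46 ECS points.

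**4. Simulation.** Assumptions: normal scores with SD 1, true difference 0.65, correlation 0.5 to 0.7 between pre-RT and 2-week ECS, and logistic dropout with slope 1.5 per SD of worse ECS. Very large samples give the expected values. Power uses 45 per arm less the missing share.

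| Missing, control / ES-IMRT | Dropout depends on pre-RT ECS | Dropout depends on 2-week ECS |
|---|---|---|
| 20% / 10% | 0.58 to 0.60, power about 73% to 75% | 0.54 to 0.55, power about 72% |
| 10% / 20% | 0.70 to 0.72 | 0.75 to 0.76 |
| 15% / 15% | 0.65 | 0.65 |

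Power follows from the responders' own SD, which selection also shrinks. For dropout on the 2-week score that SD is about 0.92, so the standardised effect is 0.54/0.92 = 0.59.

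**5. What baseline adjustment returns.** Adding pre-RT ECS as a covariate restores 0.65 when dropout depends on pre-RT ECS. When dropout depends on the unseen 2-week score, it recovers about 20% to 45% of the bias at correlations of 0.5 to 0.7, and less at weaker ones.

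For power at 38 per arm, the residual SD is √(1 − r²):

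- r = 0.3: 0.65/√0.91 = 0.681, power about 83%.
- r = 0.5: 0.65/√0.75 = 0.751, power about 90%.

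The unadjusted test has 80%.

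**The case against.** The strongest reply is that the protocol names a test for one fixed time point and sizes the trial for that same test. How to handle a missing score, a death before the visit or a patient who never starts RT is commonly left to an SAP, which is not at hand. A t-test can also be run on imputed data. This stands as far as it goes: the absence of those rules is not a fault of the protocol. It does not cover the stated choice of a primary method without the baseline score, when the protocol names a fuller method for the other scores.

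Safeguards also count. Forms may be taken by telephone, patients unable to give survey responses are excluded, and life expectancy must exceed 3 months. These reduce missing forms but do not remove them, and the protocol itself allows for 15%.

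The proposed model has limits too. It corrects fully only when dropout depends on observed scores. Section 9.0 puts the 2-week visit before any systemic treatment, so the 4- and 8-week scores may reflect such treatment. That is a reason to rely mainly on the pre-RT score.

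A reader might also infer that the t-test breaks the intention-to-treat statement. It does not: the protocol explains that principle as analysis by assigned group, and a t-test on responders by assigned arm meets that wording. It falls short only of the broader sense in which every randomized patient counts.

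**Conclusion.** The point holds as a weakness in a stated method, worth changing. The primary test leaves out a scheduled baseline score and gives no weight to patients without the 2-week form. The estimate can shift by about 0.05 to 0.11 SD either way under a 20%/10% split, which is assumed, as are the dropout slope and the correlations.

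Three stronger readings are not supported:

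- **That dropout will shift the estimate.** Missingness must be tied to the score and must differ by arm, in rate or in who is missing. Equal dropout under the same mechanism gives no bias.
- **That the protocol expects 15% to die, fall too ill or never start RT.** It does not define non-responder. That these patients have no usable score is an inference from the arithmetic; the reasons are not given.
- **That power would fall to 66%.** This is the figure for an effect of 0.55 with the SD held at 1. The selection that lowers the difference also narrows the responders' SD, and power is then about 72% to 75%.

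**What to change.** In section 10.5, make the primary test the arm difference in the ECS at 2 weeks from a linear mixed-effects model with pre-RT ECS, visit, arm by visit and dose stratum, including every randomized patient with any ECS score. ANCOVA of the 2-week ECS on pre-RT ECS and dose stratum is a simpler alternative. It does not bring in patients without the 2-week form, but it still removes bias that acts through the pre-RT score. Add one sensitivity analysis for scores missing not at random or because of death, for example a rank test that gives them the worst rank. Word the interim ECS test in section 10.6 to match, and make the change before any comparison by arm is seen.

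The cost is wording and some analysis time. No visits, forms or patients are added, and 90 stays. The downside is reliance on a model and on a missing-at-random assumption, which the sensitivity analysis is there to probe.

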### **2.1 Endpoints**

#### **Primary Endpoint:**

1. Esophageal quality of life
  - Measured by the Esophageal Cancer Subscale (ECS) of the FACT-E

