### **3.0 STUDY DESIGN**

This study is designed as a randomized phase III study. Patients will be randomized between standard of care palliative thoracic RT vs. ES-IMRT.

Patients will be stratified by intended dose prescriptions of 30 Gy in 10 fractions or 20 Gy in 5 fractions, and the choice of dose is pre-specified before randomization.

Patients will be randomized in a 1:1 ratio to either:

**Arm 1: Standard Radiotherapy (delivered as 3-D conformal radiotherapy without esophageal sparing).** An APPA technique is preferred.

**Arm 2: Esophageal Sparing Radiotherapy using IMRT.** Patients will receive the same pre-specified dose, but with esophageal sparing.

**In either arm, radiotherapy must begin no later than 2 weeks from the time of randomization, although treatment as early as possible is highly encouraged.**

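### The primary t-test is valid and correctly sized, but it leaves baseline ECS and the dose stratum unused and so gives up precision that could be had at no cost

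*Protocol*

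**What the plan says.** Section 2.1 of the protocol defines the primary endpoint as esophageal quality of life, "Measured by the Esophageal Cancer Subscale (ECS) of the FACT-E", and the schema places it 2 weeks after radiotherapy. Section 10.5 fixes the test: the 2-week FACT-E scores are tabulated, "with differences between groups tested using the Student's t-test". It names neither a covariate nor a stratum. I read the FACT-E scores there as the ECS, in line with section 2.1.

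Section 10.4 sizes the trial for the same kind of test: two-sided, independent samples, alpha 0.05, power 80%, standardised effect 0.65 and 15% non-response, giving 90 patients (45 per arm). It describes the aim as "to detect a clinically relevant ECS change in the experimental arm".

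Two pieces of information exist by design and are not used in the primary test:

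- **Baseline ECS.** Appendix 2 marks the FACT-E in the pre-RT column. Section 10.6 relies on it for a monitoring rule based on a 2-point ECS change from baseline.
- **Dose stratum.** Section 10.3 states: "The sample size calculated allows for one stratification factor at randomization, which will be the prescribed dose".

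For other endpoints, section 10.5 goes further. Survival gets a stratified log-rank test, and for the additional quality-of-life endpoints "Treatment arm differences will be analyzed using linear mixed-effects models".

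On the timing of baseline, Appendix 2 says only pre-RT, and the mandatory list in section 5.0 does not include the questionnaires. Section 3.0 says that "radiotherapy must begin no later than 2 weeks from the time of randomization".

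**The concern.** A baseline measurement of the outcome is usually one of the best predictors of the later score. Adjusting for it removes the part of the outcome variance that it explains. A t-test on the 2-week score alone keeps that variance in the standard error. With about 38 evaluable patients per arm, a chance difference between arms in baseline swallowing or appetite is not unlikely, and the planned test has no means of taking it into account.

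The dose stratum raises a related but smaller point. Stratified randomisation balances dose between the arms. If dose also predicts 2-week ECS, a test that ignores it uses a standard error larger than the design warrants.

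At stake is power that could be gained from data already scheduled for collection. The gain also depends on a clean baseline score, that is, one given before the patient knows the arm.

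**Working it through.** **Inputs.** From section 10.4: effect 0.65 SD, two-sided alpha 0.05, power 80%, non-response 15%, 45 per arm. Assumed, because the protocol gives no value: the correlation r between baseline and 2-week ECS, and the share of ECS variance explained by dose.

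**Step 1: the plan's own figure.** By the normal approximation, n per arm = 2 × (1.960 + 0.842)² / 0.65² = 37.2, rounded up to 38. Allowing for non-response, 76 / 0.85 = 89.4, rounded up to 90. This matches the protocol. The exact t calculation gives 38.14, rounded up to 39 per arm and 92 in total, a trivial difference.

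**Step 2: power of the planned test.** Evaluable patients per arm: 45 × 0.85 = 38.25. The noncentrality is 0.65 × √(38.25/2) = 2.84, and the noncentral t distribution gives power of 80.1%. The planned test delivers what section 10.4 promises.

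**Step 3: power after adjusting for baseline.** ANCOVA reduces the residual SD to SD × √(1 − r²), so the effect in residual SD units is 0.65 / √(1 − r²). With 38.25 per arm:

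| Assumed r | Variance removed (r²) | Effect in residual SDs | Power |
|---|---|---|---|
| 0 (t-test) | 0% | 0.650 | 80.1% |
| 0.1 | 1% | 0.653 | 80.5% |
| 0.2 | 4% | 0.663 | 81.7% |
| 0.3 | 9% | 0.681 | 83.7% |
| 0.4 | 16% | 0.709 | 86.5% |
| 0.5 | 25% | 0.751 | 90.0% |
| 0.6 | 36% | 0.813 | 93.9% |

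Taking exactly 38 per arm, and 76 − 4 = 72 degrees of freedom to pay for the covariates, changes these by no more than about 0.4 points (for example 83.4% at r = 0.3, 89.8% at r = 0.5 and 93.7% at r = 0.6).

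**Step 4: chance imbalance in baseline ECS.** With 38 per arm, the difference in baseline means has an SD of √(2/38) = 0.229 baseline SDs. The probability that it exceeds 0.25 SD in either direction is 2 × [1 − Φ(0.25/0.229)] = about 28%.

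**Step 5: ignoring the dose stratum.** If dose explains a share R² of the ECS variance and is balanced by design, the true two-sided alpha of the unadjusted test is about 2 × [1 − Φ(1.96/√(1 − R²))]. That is 0.044 at R² = 5%, 0.039 at 10% and 0.028 at 20%. At R² = 0 there is no effect.

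**Step 6: timing of baseline.** Section 6.5 requires an enrollment form before randomisation, but the protocol does not show what is in it. The arm is then sent to the site. Section 3.0 allows up to 2 weeks from randomisation to the start of radiotherapy, and no blinding of patients is described. A questionnaire completed in that interval satisfies the pre-RT label in Appendix 2.

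**The case against.** The strongest reply is that nothing here is wrong. Sections 10.4 and 10.5 use the same kind of test, the sample size reproduces, and the t-test is unbiased under randomisation. Chance baseline imbalance is part of the sampling variation that its standard error already covers. All of that stands. Two stronger readings are therefore unsupported: that the primary result would be biased or invalid, and that the trial is underpowered for its planned test.

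The reply continues that the gain rests on an assumed r. The endpoint targets acute effects of radiation that arise after baseline, so a weak correlation is plausible, and at r of 0.2 or less the gain is under 2 points of power. This also stands, and it is why the low values are in the table.

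On dose, stratified permuted blocks already limit imbalance. Omitting the stratum matters only if dose predicts ECS, and any effect is then conservative. It does not raise the false-positive rate.

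A reader might take the word change in section 10.4 to mean that a change-score test is intended. Section 10.5 plans no such test, so its power is not at issue. A reader might also treat the mixed models planned for secondary quality of life as a substitute for ANCOVA. Section 10.5 does not say how those models handle baseline or dose. A model over several visits would make different missing-data assumptions and include visits after systemic therapy may have begun (section 9.0).

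Finally, the documents do not show that baseline forms are completed after allocation; they only fail to prevent it. If it did happen, the t-test on 2-week scores would be untouched, whereas ANCOVA would use a covariate that may be affected by knowing the arm. This is a reason to fix the timing together with the model, not a reason to ignore baseline.

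An SAP, which was not available for this review, could add a supporting adjusted analysis. The protocol itself, however, names the unadjusted test for the primary endpoint.

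**Conclusion.** The point holds as a recommendation to improve efficiency. The planned test is valid, unbiased and sized as stated, but it sets aside a scheduled baseline score and the one stratification factor. The benefit of adjustment ranges from negligible (80.5% against 80.1% power at r = 0.1) to substantial (90.0% at r = 0.5 and 93.9% at r = 0.6). It assumes about 38 evaluable patients per arm, a true difference of 0.65 SD of the 2-week score and a linear relation with baseline. Which end of the range applies cannot be read from the protocol. The gain from the dose term is likewise conditional on dose predicting ECS. Because adjustment needs no extra patients and costs almost nothing even at low r, it should be made. The gap in baseline timing is a permission left open by the wording, not a demonstrated fault.

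**What to change.** 1. In section 10.5, make the primary analysis an ANCOVA of 2-week ECS with arm, baseline ECS and dose stratum as terms, and report the adjusted difference between arms with its 95% confidence interval. Keep 90 patients, and retain the Student's t-test as a sensitivity analysis.
2. In section 5.0, add the baseline FACT-E, FACT-L and EQ-5D to the mandatory list, to be completed before randomisation. Use the same wording in the pre-RT column of Appendix 2, and have the enrollment form in section 6.5 confirm completion.
3. Section 10.6 names the same t-test for the interim look at ECS; state whether that stays as it is.

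The cost is protocol wording and moving one form, already scheduled, ahead of the randomisation call. No new data and no further patients are needed. The change should be made before any comparison of outcomes by arm has been seen.
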